## Abstract

**Background:**

After diagnosis of a dementing illness, patients and their spouses have many concerns related to the disease and their future. This often leads to poor psychological well-being and reduced health-related quality of life (HRQoL) of the family. Support for self-management skills has been proven to be an effective method to improve prognosis of asthma, heart failure and osteoarthritis. However, self-management interventions have not been studied in dementia. Therefore, our aim was to examine, in an objective-oriented group intervention, the efficacy of self-management support program (SMP) on the HRQoL of dementia patients and their spousal caregivers as well as on the sense of competence and psychological well-being of caregivers.

**Methods:**

During the years 2011 to 12, 160 dementia patients and their spouses will be recruited from memory clinics and randomized into two arms: 80 patients for group-based SMP sessions including topics selected by the participants, 80 patients will serve as controls in usual community care. Sessions may include topics on dementia, community services, active lifestyle and prevention for cognitive decline, spousal relationship, future planning and emotional well-being. The patients and spouses will have their separate group sessions (ten participants per group) once a week for eight weeks. Main outcome measures will be patients’ HRQoL (15D) and spousal caregivers’ HRQoL (RAND-36), and sense of competence (SCQ). Secondary measures will be caregivers’ psychological well-being (GHQ-12) and coping resources, patients’ depression, cognition and signs of frailty. Data concerning admissions to institutional care and the use and costs of health and social services will be collected during a two-year follow-up.

**Discussion:**

This is a ‘proof-of-concept’ study to explore the efficacy of group support for self-management skills among dementia families. It will also provide data on cost-effectiveness of the intervention.

**Trial registration:**

ACTRN12611001173987

## Background

Cognitive disorders, such as Alzheimer disease, gradually leading to the dementia syndrome are the most important chronic illness group leading to increased need for assistance, disability and institutional care among older people
[1]. Dementia also augments stress and burden, and reduces quality of life (QoL) among caregivers
[2]. Usually, dementia patients wish to live at home as far as possible and the spousal caregivers are in the key role in enabling it. Therefore, there is an urgent need for developing supportive methods for coping, as well as effective psychosocial rehabilitation for patients with dementia and their caregivers alike.

Today, there is growing evidence that the most effective interventions for dementia are psychosocial interventions focusing on the needs of both patient and caregiver. Using these interventions, dementia families are provided with means to adapt and cope with dementia
[3]. Psychosocial interventions coach caregivers to help patients to use their remaining capacities to participate. Effective psychosocial interventions are built on co-operation between professionals and dementia families
[4]. By supporting mastery, self-efficacy and problem-solving skills of caregivers, these interventions aim to empower dementia families to cope with their everyday life, promote dignity and autonomy
[5]. Also, the concept of reciprocity in giving and receiving support has been highlighted
[6]. Many psychosocial studies demonstrate that individuals can be supported to maintain their skills and build resilience
[4,7,8].

Many health-promoting programs have used self-management methods and they have been shown to be effective in improving prognosis of chronic diseases including asthma,diabetes, and heart failure
[9,10]. Self-management can be defined as a person’s ability to organize his/her life under the influence of a chronic disease, to engage in activities and protect and promote health through knowledge. Self-management programs (SMP) combine biological, psychological and social intervention techniques to maximize functioning
[9,11]. In SMP, professionals support patients with a patient-centered approach to manage their care
[12,13]. This includes support of patient’s autonomy, decision making, problem-solving skills and responsibility
[5,12,14]. It places patient’s values, needs and priorities in the center of health care
[15]. In SMP, health professionals act as coaches or collaborators - partners - rather than as experts, and they respect the patients’ everyday know-how. Central concepts are patient’s empowerment, support of self-efficacy and mastery
[12].

Self-management has been less studied in the context of dementia although many trials examining psychosocial support have included features of self-management, elements like family-centered services, respecting autonomy of caregiving families, empowering caregivers and developing cooperation
[4,8,16]. In a Finnish SMP, the dementia patients and their spousal caregivers are seen as experts of their own life and consequently expected to take an active role regarding their health and illness
[4,5]. SMP differs from traditional knowledge-based education; it includes dimensions such as helping patients and their caregivers to identify the problems, developing their own problem-solving skills and improving their self-efficacy to master their everyday life. Professionals’ optimistic orientation is the basement in SMP
[4,5].

Earlier, the diagnosis of dementing illness was often associated with hopelessness and stigma. Nowadays, the dementia is settled earlier during the course of the disease. Thus, patients are cognitively more capable to cope with the disease. Professionals are required to give more emotional support, and provide patients also with practical skills and techniques. Often the patients have few opportunities to talk about their worries after the disclosure of diagnosis
[17]. SMP intervention should be centered on patient and carers alike
[18].

A recent paper described an English model of SMP for dementia patients and their caregivers
[19]. The model included previous elements of psychosocial interventions and health promotion. SMP supported families to be physically, mentally and socially active, and it promoted knowledge for understanding and managing with dementia
[19]. Facilitators guided the SMP groups of patients and caregivers to select the most relevant topics and assisted participants to explore them
[19].

In the present study, we examine the self-management program (SMP) method among couples with dementia in a clinical trial. It is based on evidence-based knowledge of dementia care and healthy well-being. The aim is to examine the effectiveness of SMP in an objective-oriented group intervention, including empowerment of participants, support of their mastery and self-efficacy. The primary aim is to explore the effects of intervention on dementia patients’ QoL and on spousal caregivers’ QoL, sense of competence and psychological well-being. The secondary aims are to assess the effects of group intervention on patients’ depression, cognition and signs of frailty and on caregivers’ depression and self-efficacy. We also study the effects of intervention on the use and costs of health care services, dementia patients' time to be at home and mortality.

## Methods

### General design

This is a randomized, controlled, prospective intervention trial to examine the effectiveness of the SMP using objective-orientated group intervention where participants’ empowerment, mastery and self-efficacy are supported.

The intervention period lasts for two and a half months, and is compared with usual care. The study protocol and its amendments were approved by the Ethics Committee of Helsinki University Central Hospital (decision number 340/13/01/2010, 3/2011 and 8/2011) and by the chief executive of the Health Centre of the City of Helsinki. Informed consent was obtained from each patient and/or their spousal caregiver before any study procedures. An executive committee ([name], [name]) is responsible for the planning, conducting and monitoring of the study.

### Participants

The recruiting has started in 2011 from memory clinics and from private neurologists’ or geriatricians’ consultation offices in the greater Helsinki area (Helsinki, Espoo, Vantaa). Patients who have received dementia diagnosis after full diagnostic procedures recommended by the Finnish national guidelines
[20] (fulfilling criteria for probable Alzheimer disease diagnosis according to NINCDS-ADRDA Alzheimer’s criteria) and who live at home with their spouse are eligible to be recruited to the study.

Other inclusion criteria are:

Finnish speaking

living in the greater Helsinki area (Helsinki, Espoo, Vantaa)

not in the terminal phase of illness (estimated prognosis > one year)

is able to move independently (with or without devise)

no severe hearing loss that impedes participation in the group

the ability to concentrate in a group situation for two hours without a spousal caregiver

Those couples fulfilling the inclusion criteria are invited to take part in this intervention study. The information sheet about the study is given to the couple in the memory clinic or when visiting a private specialist after diagnostic procedures. A study nurse interviews the couple by phone to makes sure that they fulfill the inclusion criteria. After this, oral information about the study is given, and an appointment is made for the first visit. At the beginning of the first visit, the couples are given written and oral information of the study and both are asked to sign an informed consent. In the case of the dementia patient’s poor capability of judgment, the spousal caregiver gives a proxy’s consent for both spouses.

### Study procedures

The baseline visit lasts about one hour and includes interviews of both spouses and collection of demographic data, diagnoses, current medications, and baseline use of health and social services. Diagnoses and medications are confirmed from medical records provided by the couples. Charlson’s comorbidity index is calculated to assess the severity and prognostic value of the participants' disease burden
[21].

Health-related quality of life (HRQoL) of the patients is assessed by using the 15D instrument
[22]. Dementia patients are also assessed with the Clinical Dementia Rating Scale (CDR)
[23], the Mini Mental State Examination (MMSE)
[24], verbal fluency
[25], and the clock drawing test
[26]. Other measurements include activities of daily living (ADL)
[27], instrumental activities of daily living (IADL)
[28], the Mini Nutritional Assessment (MNA)
[29], Cornell depression test
[30], Illness Cognition Questionnaire
[31], frailty criteria
[32], and the Psychosocial Well-being Scale
[33]. The presence of advance directives, such as a living will, are inquired about. Clinical measurements include height, weight, blood pressure and hand grip strength.

The spousal caregivers are asked questions concerning the impact of their spouse’s dementia diagnosis and they are assessed by the RAND-36 HRQoL instrument
[34,35], 12-item General Health Questionnaire (GHQ-12)
[36], the Center for Epidemiologic Studies Depression Scale (CES-D)
[37], Pearlin Mastery Scale for their personal coping resources
[38], and the Sense of Competence Questionnaire (SCQ)
[39]. Their weight and blood pressure is also assessed on each visit.

The couples are randomized in clusters of 20. After acquiring informed consent to the study and assessing 20 couples with eligibility criteria, the randomization is performed by telephone to a randomization center. Couples are randomly allocated by means of computer-generated random numbers. Every randomization result will appear in the program after the participants name has been written and the person executing the randomization has confirmed the process with her initials. This ensures that neither the study nurse, nor person doing the randomization can influence the result. Half of the participants are randomized to the rehabilitation group (intervention group) and the other half receives usual care (control group).

We aim for a total of 160 couples to be randomized in two groups: group rehabilitation as the intervention and normal care as the control group. Participating couples are assessed by two study nurses three times over nine months: at baseline, three, and nine months. Use of health services, institutionalizations and mortality of both patients and caregivers will be retrieved from the central registers until 24 months from the baseline measurements. The flow chart of the study is presented in Figure
1, and the study assessment procedures are described in Table
1.

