**Figure 1 F1:**
[figure not shown]
The flow chart of the study.

**Table 1 T1:** Study assessments, procedures and timetable

**Assesment**^**1**^	**Telephone interview**	**Baseline visit**	**3-month visit**	**9-month visit**	**At 24 months**
Patient					
Inclusion criteria	X				
Demographics, diagnoses, drugs, background information		X	X	X	
CDR, MMSE, verbal fluency, clock drawing test		X	X	X	
Grip strength, blood pressure and pulse		X	X	X	
MNA		X	X	X	
Weight, BMI		X	X	X	
ADL, IADL		X			
Cornell Depression Scale		X	X	X	
Illness Cognition Questionnaire		X	X	X	
15D QoL		X	X	X	
Use of health and social services, mortality			X	X	X
Psychosocial well-being scale		X	X	X	
Spousal caregiver	X	X	X	X	
Demographics, diagnoses, drugs, questions related to coping with dementia		X	X	X	
Psychosocial well-being scale		X	X	X	
Grip strength, blood pressure and pulse		X	X	X	
Weight, BMI		X	X	X	
Sense of competence, SCQ		X	X	X	
CES-D		X	X	X	
12-GHQ		X	X	X	
Pearlin Mastery Scale		X	X	X	
Rand-36 QoL		X	X	X	
Use of health and social services, mortality			X	X	X

^1^*CDR* Clinical Dementia Rating Scale
[23] (0.5 suggests possible dementia, 1 mild, 2 moderate, and 3 severe dementia), *MMSE* Mini Mental State Examination
[24]. *MNA* Mini Nutritional Assessment
[29] (<24 suggests risk for malnutrition or malnourishment); *BMI* body mass index; *ADL* activities of daily life
[27]; *IADL* instrumental activities of daily living
[28]; Cornell Depression Test
[30]; Illness Cognition Questionnaire
[31]; 15D QoL, measure of health-related quality of life
[22]; Psychosocial Well-being Scale
[33]; *SCQ* Sense of Competence Questionnaire -
[39]; *CES-D* The Center for Epidemiologic Studies Depression Scale
[37]; 12-*GHQ*, 12-item General Health Questionnaire. Pearlin Mastery Scale
[38];Rand-36 QoL
[34,35].

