### Outcome measurements

Primary outcome measures are changes in patients’ HRQoL assessed by 15D
[22] and in spousal caregivers’ HRQoL assessed by RAND-36
[35], sense of competence assessed by SCQ
[39]. Secondary outcome measures are patients’ time spent at home and changes in patients’ depression (Cornell)
[30], and feelings of acceptance and helplessness assessed using subscales of the Illness Cognition Questionnaire
[31] and cognition (verbal fluency, the clock drawing test (CDT))
[25,26]. Secondary outcome measures for caregivers are psychological well-being assessed by 12-GHQ
[36] and personal coping resources by the Pearlin Mastery Scale
[38] and also changes in depression will be measured by CES-D
[37]. Weight, blood pressure and hand grip are measured as secondary outcomes in the couples. Total mortality, use and costs of health care and social services of both spouses as well as cost-effectiveness of the intervention are measured up to 24 months from the beginning of the baseline measurements.

The study is made in co-operation with the Health Care Centre and Social Services Department of the City of Helsinki, the University of Helsinki, the Central Union for the Welfare of the Aged, and the Rehabilitation Hospital of Oulunkylä.

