### Statistical analyses

Sample size was calculated based on the 15D measure
[22]. With an estimated standard deviation of 0.10, and type I error of 5%, and 80% power, 62 patients would be needed in each group to show a 10-point difference between groups. We estimated that 20% will drop out so we decided on 160 patients as a sample size. Data will be analyzed on an intention-to-treat basis. In baseline findings, the continuous variables and descriptive values will be expressed by means with standard deviations (SD) and medians with range. For the variables with a normal (Gaussian) distribution, statistical comparisons between the groups will be made by using an analysis of variance. If the variables have a non-normal distribution or ordinal level, statistical comparison between groups will be made using the Mann–Whitney U test. Measures with a discrete distribution will be expressed as percentages (%) and analyzed by chi-square or Fischer's exact test when appropriate. Imputation method of ‘the last observation carried forward’ (LOCF) and ‘worst-rank score’ principle will be used.

Since the distributions of health care costs are highly skewed, the differences between means and confidence intervals are estimated using the bootstrap method (bias corrected and accelerated bootstrapping).

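### Baseline service use is collected according to the text but unmarked in Table 1, and the cost comparison as described leaves it unused, which may cost some precision but does not bias the result

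*Protocol article*

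**What the plan says.** All of this is in the Methods of the protocol article.

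- **Study procedures, baseline visit.** The interviews with both spouses cover, among other items, "baseline use of health and social services".
- **Table 1.** The row "Use of health and social services, mortality" appears once in the patient block and once in the caregiver block. Each time it is marked at 3, 9 and 24 months and not at the baseline visit.
- **Study procedures, follow-up.** Use of health services, institutionalizations and deaths of both spouses "will be retrieved from the central registers until 24 months from the baseline measurements". Social services are not in that list.
- **Outcome measurements.** The 24-month outcomes include "use and costs of health care and social services of both spouses as well as cost-effectiveness of the intervention".
- **Statistical analyses.** Because costs are highly skewed, "the differences between means and confidence intervals are estimated using the bootstrap method", in its bias-corrected and accelerated form. No baseline term is named for this comparison, and none is ruled out.

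**The concern.** There are two linked points.

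First, the article makes two statements about one data item that do not agree. Study procedures sends the reader to Table 1 for the assessment schedule, so anyone working from the table would find no instruction to record service use at baseline for either spouse. A baseline value missed at the visit may be hard to replace, at least for social services.

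Second, the cost outcome is one where a few heavy users can move a mean, and the article itself calls the distributions highly skewed. With 80 couples per arm, a chance imbalance in prior use can carry into the observed cost difference and so into the cost-effectiveness result. The trial intends to collect the variable best placed to absorb that imbalance, yet the comparison as described makes no mention of it. At stake are the width of the cost interval and the robustness of the estimate to an unlucky allocation.

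**Working it through.** **Step 1. Is the mismatch real?**

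| Item | Study procedures | Table 1, patient | Table 1, caregiver |
|---|---|---|---|
| Service use at baseline | collected | not marked | not marked |
| Service use at 3, 9 and 24 months | follow-up to 24 months | marked | marked |

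A fault in text extraction is unlikely. Neighbouring rows such as 15D, RAND-36 and the psychosocial well-being scale keep their baseline mark, and both service-use rows show the same pattern.

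Could another row cover it? The patient row "Demographics, diagnoses, drugs, background information" is marked at baseline and could be read broadly, but it does not name service use, which has a row of its own. The matching caregiver row has no background-information wording and refers instead to questions on coping with dementia. The mismatch therefore stands for both spouses, most clearly for the caregiver.

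**Step 2. What could adjustment gain?**

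The article gives no cost SD, target cost difference, interval width or baseline-to-follow-up correlation, so there is no figure of its own to reproduce. The one input that matters, r, is an assumption and is shown over a range.

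Formula: width of adjusted interval / width of unadjusted interval ≈ sqrt(1 - r²).

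| r (assumed) | sqrt(1 - r²) | Interval narrower by |
|---|---|---|
| 0 | 1.000 | 0% |
| 0.1 | 0.995 | 0.5% |
| 0.2 | 0.980 | 2.0% |
| 0.3 | 0.954 | 4.6% |
| 0.4 | 0.917 | 8.3% |
| 0.5 | 0.866 | 13.4% |
| 0.6 | 0.800 | 20.0% |
| 0.7 | 0.714 | 28.6% |

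For example, at r = 0.5: 1 - 0.25 = 0.75, and sqrt(0.75) = 0.866.

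**Step 3. Does the formula survive skewed costs at this sample size?**

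The plan randomizes 160 couples, 80 per arm. Lognormal baseline and follow-up costs with no arm effect were simulated 4,000 times for each log-scale correlation. The empirical standard error of the difference adjusted for baseline cost was divided by that of the raw difference in means.

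| Log-scale correlation | Realised r on cost scale | SE ratio, simulated | sqrt(1 - r²) at realised r |
|---|---|---|---|
| 0 | about 0 | 1.004 | 1.000 |
| 0.3 | 0.22 | 0.970 | 0.975 |
| 0.5 | 0.40 | 0.919 | 0.917 |
| 0.7 | 0.61 | 0.762 | 0.792 |

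The formula is a fair guide. When baseline cost predicts nothing, the extra covariate costs about 0.4% in standard error.

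**The case against.** The strongest reply concerns the analysis. The article gives costs one sentence and does not say the comparison will be unadjusted. A condensed article may leave covariates to an analysis plan that is not shown, and a BCa bootstrap can be applied to an adjusted difference just as well as to a raw one. This stands. A reader might infer that the trial has decided against using baseline data, but the text supports only that the stated comparison does not mention them.

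A reader might also infer that the unadjusted comparison is wrong. It is not. Randomization makes it unbiased, and its interval already allows for chance imbalance. Nor do the documents support a claim that the interval is wider than it needs to be by a known amount. A low r is plausible. Patients live at home at entry, so later institutional care cannot show in their baseline use. Couples are approached after diagnostic procedures, so recent use may largely reflect the work-up.

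On the table, it can be said that Table 1 is a summary and not a case report form. Other baseline items named in the text, such as advance directives and the comorbidity index, have no row either. Pairing service use with mortality also suggests a row meant for follow-up outcomes. That may explain the empty cell, and it means that non-collection cannot be inferred. It does not remove the conflict, because service use does have its own row and that row omits a visit at which the text requires it.

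Finally, costs are not a primary outcome, and the sample size rests on 15D. No primary conclusion depends on this point.

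**Conclusion.** The concern holds in a limited form.

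- **Firm:** the text and Table 1 disagree on whether service use is recorded at baseline, for both spouses, and must be reconciled. The registers cannot be assumed to be a complete fallback, since the retrieval as described names health services but not social services. Whether they also hold social-service data cannot be settled from the article.
- **An improvement, not the correction of an error:** using baseline use or cost in the cost comparison. The benefit is precision and protection against chance imbalance, not validity. Its size depends on an undocumented r: negligible at 0.2 or below (0 to 2%), modest at 0.3 (about 5%) and worthwhile at 0.5 (about 13%).

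The adjustment is worth making because the data are already meant to be collected and the simulated penalty is trivial if r proves to be near zero.

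**What to change.** 1. In Table 1, mark service use at the baseline visit for patient and caregiver, preferably in a row separate from mortality. State one fixed look-back period, the same for all couples. Recruitment is still open, so this helps couples yet to enter.
2. State the source of the baseline value for each component. Registers may supply prior health-service use. Unless they are confirmed to hold social services too, prior social-service use should come from the baseline interview.
3. In Statistical analyses, estimate the cost difference from a regression of follow-up cost on arm and baseline service use or cost. Apply the BCa bootstrap to the adjusted difference and resample couples, so that both spouses' costs stay together.
4. Keep the unadjusted difference in means, with its own BCa interval, as a sensitivity analysis.

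The cost is a table correction, one covariate, a sentence or two of text, and some work to put prices on baseline use if cost rather than use is the covariate. The sample size does not change.
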